**Outcomes**

The primary outcome will be measured after 6 months by evaluating change in cognitive performance by using PGI Memory Scale total score. Improvements in cognitive domains including executive functioning, processing speed, attention, and memory will be recorded. Secondary outcomes including change in functionality and quality of life will be measured using Barthel's ADL Index, Lawton's Scale, and SF-36 respectively. By utilization of the visual paired associates test, immediate and delayed recall, logical memory immediate and delayed recall, word list learning and delayed recall will be reassessed for noticing changes in the memory domain. Adverse events such as presence of psychological stress, musculoskeletal pain, or injury will be recorded. An external safety committee will regularly assess safety-related issues throughout the duration of the study.

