**Intervention**

The group imparted with computer-based customized training using RehaCom software will be assessed using Neuropsychological Test Battery (NTB) including, PGI- Memory Scale, Wisconsin Card Sorting Test, Stroop Color and Word Test. Stroop Color and Word Test will assess the relative speed of reading the names of colors and identifying the colors correctly that are printed in another color. It comprises of an interference component because it requires the participant to exhibit a reading response. The advantage of using this test is that it measures the ease with which a person can shift his perceptual set to adapt to changing demands, and to inhibit the usual response from interfering with the unusual one. This test is a measure of two essential characteristics: cognitive flexibility and response inhibition. Moreover, the PGI memory scale will be used to measure verbal and nonverbal memory. The ten sub-tests measure different memory domains such as, remote memory, recent memory, mental balance, attention and concentration, delayed recall, immediate recall, retention for similar pairs, retention for dissimilar pairs, visual retention, and recognition. Furthermore, cognitive training will include assessment of abstract reasoning and mental flexibility using the Wisconsin Card Sorting Test. The subjects can classify cards according to the color, shape of its symbols, or the number of the shapes shown on each card. With a change in the classification rule every 10 cards, it is expected that once the participant has figured out the rule, he/she will start making mistakes with an alteration in rules. This task fundamentally measures how well people can adapt to the changing rules.

Comprehensive geriatric assessment will be carried out using the Charlson Comorbidity Index, the Barthel ADL Index, IADL Scale, the Kuppuswamy scale for socio-economic status, GDS-15 for assessment of depressive symptoms, Mini-Cog for cognitive functioning, and ICIQ for determining the presence of urinary continence in subjects.

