**Analysis Plan**

Data will be entered and analyzed using STATA software. Neuropsychological Test Battery (NTB) total score and the z-scores for executive functioning, processing speed, and memory will be calculated. For computing the NTB total score, at least 8/14 NTB components will be needed; at least 3/5 test scores for the executive functioning domain, 3/6 test scores for the memory domain, and 2/3 test scores for evaluating processing speed. Mixed-model repeated-measures analyses having a maximum likelihood estimation will be used to analyze changes in cognitive performance as a function of randomization group (dichotomous variable coded as 0 for control and 1 for intervention), time (continuous variable coded as 0 for baseline, 6-month visit, characteristic, and group × time × characteristic interaction. The characteristics will be either dichotomous (sex, presence of nutritional risk, and deterioration in quality of life) which will be dichotomized depending on the median value) or continuous variables (age, education level, scores on the following scales: MMSE, Mini-Cog, BADL, IADL, GDS-15, SF-36, and MNA). Log-transformation will be appropriately applied to the skewed continuous variables.

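### The declared primary outcome, the PGI Memory Scale total score, is not named in the Analysis Plan, which defines a different composite (a 14-component NTB total) and leaves the model's outcome unspecified

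*Protocol*

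**What the plan says.** The protocol's Outcomes section fixes instrument and time point: "The primary outcome will be measured after 6 months by evaluating change in cognitive performance by using PGI Memory Scale total score". The same section lists further memory tests to be repeated: "By utilization of the visual paired associates test, immediate and delayed recall, logical memory immediate and delayed recall, word list learning and delayed recall".

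The Intervention section describes the battery as "Neuropsychological Test Battery (NTB) including, PGI- Memory Scale, Wisconsin Card Sorting Test, Stroop Color and Word Test", and says that the PGI scale has ten sub-tests, all presented there as covering memory domains.

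The Analysis Plan does not mention the PGI Memory Scale. The cognitive scores it derives are these: "Neuropsychological Test Battery (NTB) total score and the z-scores for executive functioning, processing speed, and memory will be calculated". It then gives completeness rules: "For computing the NTB total score, at least 8/14 NTB components will be needed", with domain minima of "at least 3/5 test scores for the executive functioning domain, 3/6 test scores for the memory domain, and 2/3 test scores for evaluating processing speed". The model is described as follows: "Mixed-model repeated-measures analyses having a maximum likelihood estimation will be used to analyze changes in cognitive performance". No instrument is named as its dependent variable.

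**The concern.** An analyst who starts from the Outcomes section would put the PGI total into the model. An analyst who starts from the Analysis Plan would build the NTB total, because that is the only overall score for which a derivation is given. These are different variables and can give different answers. The protocol does not say which one is the trial's primary result.

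The scoring rule adds to the difficulty. It is precise about counts and minimum data, but no section lists the 14 components, and the tests named elsewhere do not lead to them. If this stays open until the data are in, the headline score and its composition can both be chosen with the results in view.

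**Working it through.** **Inputs.** NTB components by domain: 5 executive, 6 memory, 3 speed; minima 3, 3 and 2; overall 8 of 14 (Analysis Plan). PGI Memory Scale: ten sub-tests; battery also includes the Wisconsin Card Sorting Test and the Stroop test (Intervention). Further memory tests: paired associates, logical memory and word list (Outcomes).

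**Step 1: the plan's own counts.** 5 + 6 + 3 = 14, and 3 + 3 + 2 = 8. Both agree with the stated totals, so the rule is consistent within itself. The question is whether it fits the outcome and the tests.

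**Step 2: can the NTB total be the PGI total?**
- With all components present, executive and speed scores make up 5 + 3 = 8 of 14, and memory scores 6 of 14 (43%). A PGI total contains no card-sorting or Stroop score.
- If the PGI sub-tests enter separately as memory scores, ten do not fit six places.
- If all ten are placed anywhere among the 14, then 14 − 10 = 4 components remain for card sorting and Stroop. As the protocol presents all ten as memory sub-tests, those 4 would have to fill 8 executive and speed places.
- If the PGI total enters as one score, it is 1 component of 14.

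Under each option the NTB total differs from the PGI total.

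**Step 3: can the rule be mapped to the named tests?** The further memory tests can be counted as 3 tests × 2 forms (immediate or learning, and delayed) = 6 scores, which is the size of the memory domain. On that count:
- they fill the domain and leave no memory place for the PGI scale, although the Intervention section puts it in the battery;
- with the PGI total added as a single score, 6 + 1 = 7 scores compete for 6 places;
- with the ten sub-tests added, 6 + 10 = 16 scores compete for 6 places.

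The count of six is an inference, because the punctuation of that sentence allows others. What does not depend on it is that the 14 components are listed nowhere and that ten PGI sub-tests do not fit the memory domain.

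**Step 4: the two sections side by side.**

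| Question | Outcomes | Analysis Plan |
|---|---|---|
| Score | PGI Memory Scale total | NTB total and three domain z-scores |
| Called primary? | Yes | No score is called primary |
| Derivation given? | No | Yes, with minimum counts |
| Dependent variable of the model | – | Change in cognition, instrument not named |

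**The case against.** The strongest reply is that the sections can be read together. Outcomes defines the primary outcome as change in cognition measured by the PGI total, and the Analysis Plan models change in cognition in nearly the same phrase. On that reading the model covers the PGI total, and the NTB scores are additional. Only the PGI total is ever called primary. The study is a pilot of 15 per group, sized on feasibility, and a list of components is the kind of detail that a separate statistical analysis plan often supplies.

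Much of this stands, and it rules out several stronger readings:
- A reader might infer that the PGI total receives no analysis at all. The text does not show that; it shows an unnamed dependent variable.
- A reader might infer that the NTB is made entirely of other tests. The Intervention section says that it includes the PGI scale, and the match of six memory scores is only suggestive.
- A reader might set the two named executive tests against the minimum of three executive scores and conclude that the domain cannot be computed. That compares instruments with scores: each test may yield several, and the battery list is worded as open.
- A reader might attach an inflated false-positive rate to two competing primary scores. The protocol calls only one score primary and states no significance level, so there is no basis for such a figure.
- A reader might object that attention has no z-score. It is covered by a PGI sub-test, and a separate score is a matter of preference.
- A mapping can be constructed: count four PGI sub-tests as executive or speed scores and take four more from card sorting and Stroop, so that 6 + 4 + 4 = 14. Nothing in the protocol states this, it goes against the description of all ten as memory sub-tests, and the result would still not be the PGI total.

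What the reply does not remove is the conflict inside the protocol. The protocol has not simply left scoring to a later document. It sets a detailed rule for a score that is not its primary outcome and is silent on the one that is.

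**Conclusion.** The point holds in this form: the primary outcome is clear in Outcomes, the Analysis Plan does not carry it through, and the only overall score it defines is a different variable. The NTB composition cannot be reconciled across Intervention, Outcomes and Analysis Plan from the text.

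The consequence is qualitative. It concerns which variable is reported as the main result, not the sample size or a calculable error rate. It matters in a pilot too, since this one declares a primary outcome and a model. That the NTB total differs from the PGI total needs no outside assumption. That the memory domain is filled by the further tests in Outcomes would be an inference, and the verdict does not rest on it. A statistical analysis plan, not available for this review, may name the dependent variable, but the protocol sections would still need to be brought into line.

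**What to change.** In the Analysis Plan:
1. State that the dependent variable of the primary mixed-model analysis is the PGI Memory Scale total score at baseline and 6 months.
2. Label the NTB total and the domain z-scores as secondary.
3. List the NTB components by domain, say whether and how the PGI scale enters, and bring the 14-component rule and its minimum counts into line with the tests actually given at both visits. If the further memory tests in Outcomes belong to the battery, name them in the battery description as well.

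The cost is protocol wording, with no extra participants or visits. The change should be made and dated before outcome data are examined.

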**Sample Size**

Since it is a pilot study, 15 participants will be recruited in each group as per feasibility. Considering 10% dropout due to loss to follow up, 17 participants will be recruited in to each group giving a total of 68 participants.

**Analysis Plan**

Data will be entered and analyzed using STATA software. Neuropsychological Test Battery (NTB) total score and the z-scores for executive functioning, processing speed, and memory will be calculated. For computing the NTB total score, at least 8/14 NTB components will be needed; at least 3/5 test scores for the executive functioning domain, 3/6 test scores for the memory domain, and 2/3 test scores for evaluating processing speed. Mixed-model repeated-measures analyses having a maximum likelihood estimation will be used to analyze changes in cognitive performance as a function of randomization group (dichotomous variable coded as 0 for control and 1 for intervention), time (continuous variable coded as 0 for baseline, 6-month visit, characteristic, and group × time × characteristic interaction. The characteristics will be either dichotomous (sex, presence of nutritional risk, and deterioration in quality of life) which will be dichotomized depending on the median value) or continuous variables (age, education level, scores on the following scales: MMSE, Mini-Cog, BADL, IADL, GDS-15, SF-36, and MNA). Log-transformation will be appropriately applied to the skewed continuous variables.

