**Methods**

**Study Design**

A randomised controlled trial would be carried out by recruiting elderly visiting the out-patient-clinic. Subjects will be randomized 1:1:1:1 to receive either computer based cognitive therapy (CBCT) based on a Germen software Rheacom, CBCT+ diet which will be created after modification of Mediterranean diet or CBCT+Diet+ Exercise regime (which will be created by experts in the field of Physiotherapy) and the control group. The intervention group will receive 6 months of intervention to have 40-44 sessions, of 40 minutes duration and the control group brain stimulating activities such as sudoku, mental maths, and learning music and new skills.

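### Maximum likelihood with about 60 evaluable participants slightly understates the residual variance; restricted maximum likelihood with small-sample degrees of freedom is a cheap, minor correction

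*Protocol*

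**What the plan says.** The Analysis Plan fixes the estimator for change in cognition: "Mixed-model repeated-measures analyses having a maximum likelihood estimation". Group enters as a "dichotomous variable coded as 0 for control and 1 for intervention", and time as "time (continuous variable coded as 0 for baseline, 6-month visit", so there are two visits. The model also takes a characteristic and a three-way interaction of group, time and characteristic.

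The Sample Size section states that "15 participants will be recruited in each group as per feasibility" and, allowing for 10% dropout, that "17 participants will be recruited in to each group giving a total of 68 participants". The Study Design section has four arms: "Subjects will be randomized 1:1:1:1".

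The protocol gives no significance level, no reference distribution for the tests and no degrees-of-freedom method.

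**The concern.** Maximum likelihood estimates the variance as if the fixed effects were known. In large trials this does no harm. With about 60 people, the parameters spent on the mean are a noticeable share of the information, so the residual variance is biased downwards. Standard errors and confidence intervals then come out too small, and tests reject a true null hypothesis more often than their nominal level. The bias grows with each term added to the mean model, and this plan adds terms by bringing in characteristics.

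At stake is the honesty of the intervals and p-values for change in cognitive performance. Because the protocol names the estimator, this is a stated choice. A separate statistical analysis plan could add a degrees-of-freedom method, but it could not adopt REML without departing from the protocol's wording.

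**Working it through.** **Inputs**
- Evaluable participants: 15 per group × 4 groups = 60 (Sample Size).
- Recruited: 17 per group, 68 in total (Sample Size).
- Visits: two, baseline and 6 months (Analysis Plan).
- Group coding: 0/1 (Analysis Plan).
- Assumed: two-sided 5% level. Both a t and a normal reference are computed, because the protocol names neither.
- Assumed: the model includes group × time. The Analysis Plan lists group, time, characteristic and the three-way term, and does not write out the lower-order interactions.

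**The plan's own figure.** 15 / 0.90 = 16.7, rounded up to 17; 17 × 4 = 68. This reproduces the stated total.

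**Number of mean parameters for change, p.** With two visits and complete data, the group × time test is a test on within-person change.
- Group × time only: mean change and group difference in change, so p = 2.
- With one characteristic: those two, plus characteristic × time and the three-way term, so p = 4.

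**Variance and standard error.** Ratio of the maximum likelihood variance to the unbiased variance = (N − p)/N.
- p = 2: 58/60 = 0.967, so the variance is 3.3% low; standard error ratio √0.967 = 0.983.
- p = 4: 56/60 = 0.933, so the variance is 6.7% low; standard error ratio √0.933 = 0.966.

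**Type I error.** Actual rate = P(|t on N − p df| > c × √((N − p)/N)), where c is 1.96 (normal) or the 97.5% point of t on N − p degrees of freedom.

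| Model, N = 60 | Reference | c × ratio | Type I error |
|---|---|---|---|
| p = 2 | t (c = 2.002) | 1.968 | 5.4% |
| p = 4 | t (c = 2.003) | 1.935 | 5.8% |
| p = 2 | normal (c = 1.960) | 1.927 | 5.9% |
| p = 4 | normal (c = 1.960) | 1.894 | 6.3% |

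**Width of the confidence interval** relative to the exact t interval, with a normal reference:
- p = 2: 0.983 × 1.960 / 2.002 = 0.963, or 3.7% too narrow.
- p = 4: 0.966 × 1.960 / 2.003 = 0.945, or 5.5% too narrow.

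With a t reference only the standard error ratio matters, so the intervals are 1.7% and 3.4% too narrow.

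**How much is due to the estimator.** REML with a normal reference gives 5.5% for both models. REML with t on N − p degrees of freedom gives 5.0%, exactly so with complete data. Changing the estimator alone therefore removes only part of the excess when a normal reference is used.

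**Check with dropout.** A simulation used a random-intercept model, 68 randomised, 10% missing at 6 months, an assumed within-person correlation of 0.6, the three active arms pooled against control, a normal reference and 8,000 runs. Type I error was 6.0% with maximum likelihood and 5.5% with REML. With a characteristic in the model it was 6.3% and 5.5%. The simulation error is about √(0.06 × 0.94 / 8,000) = 0.27 percentage points, so these agree with the formulas.

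**The case against.** The strongest reply is that the effect is too small to matter here. The trial is called a pilot and is sized on feasibility, with no power calculation and no stated decision threshold. For the model as written, maximum likelihood with a t reference costs about 0.4 points (p = 2) to 0.8 points (p = 4) of type I error. The rest of the excess, up to 6.3%, comes with a normal reference, and the protocol does not say that one will be used. The degrees-of-freedom method is a detail often left to the statistical analysis plan, so its absence cannot be held against the protocol. All of this stands, and it limits the point to a minor one. It does not remove the point, because the bias remains under a t reference.

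Two stronger readings are tempting, and the documents do not support either.

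- A reader might infer error rates of about 7% to 8%. With a normal reference, four separate arms crossed with a characteristic (p = 8, N = 60) give 7.4%. Separate fits of one active arm against control (N = 30) give 6.9%, or 8.0% with a characteristic. The arithmetic is right, but the Analysis Plan codes group as 0/1 and describes no two-arm fits. How four arms map onto a 0/1 variable is a separate question and should not be used to enlarge this one.
- A reader might infer that a later trial sized on these estimates would be too small. The protocol does not say that this variance will be used for that purpose. If it were, a 3.3% bias is minor beside the sampling error of a variance on 58 degrees of freedom, about √(2/58) = 19%.

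**Conclusion.** The concern holds as a minor correction. Followed as written, the plan understates the residual variance by 3.3% (group × time) to 6.7% (with a characteristic). At an assumed two-sided 5% level, the type I error is about 5.4% to 5.8% with a t reference and 5.9% to 6.3% with a normal one. In the normal case the intervals are about 4% to 5.5% too narrow.

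These figures rest on 60 evaluable participants, two visits, complete data and a model that includes the lower-order interactions. The direction of the bias depends on neither the reference distribution nor the exact number of completers. Nothing here suggests that the trial's conclusions would be overturned.

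**What to change.** In the Analysis Plan, replace maximum likelihood estimation with restricted maximum likelihood (REML) and a small-sample degrees-of-freedom method, for example Kenward-Roger, for all estimates, confidence intervals and tests. Both parts are needed: REML with a normal reference would still leave about 5.5% at N = 60.

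The interaction terms should then be tested with the corresponding t or F tests, since REML likelihoods cannot be compared between models with different fixed effects.

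The cost is one line of wording and slightly wider intervals. Recruitment, visits and data collection do not change.

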**Aim**

To study the effect of multimodal intervention, including cognitive training using RehaCom software, dietary counselling, and physiotherapy on improvement of cognitive function and cognitive performance in elderly, diagnosed with subjective cognitive impairment in community settings and out-patient clinics.

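### Four arms are randomised but the model codes group as 0/1, so it estimates neither the multimodal effect nor what diet and exercise add

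*Protocol*

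**What the plan says.** The Aim is "To study the effect of multimodal intervention, including cognitive training using RehaCom software, dietary counselling, and physiotherapy", that is, the effect of a package with three components.

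Study Design states: "Subjects will be randomized 1:1:1:1 to receive either computer based cognitive therapy (CBCT"), followed by CBCT plus diet and then "CBCT+Diet+ Exercise regime (which will be created by experts in the field of Physiotherapy) and the control group". The active arms are nested: each adds one component to the one before, and only the last contains all three.

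Sample Size also counts four groups: "Since it is a pilot study, 15 participants will be recruited in each group as per feasibility", raised to 17 per group and 68 in total for 10% dropout.

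Under Outcomes, the primary outcome is "change in cognitive performance by using PGI Memory Scale total score", measured after 6 months.

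The Analysis Plan gives one model: "Mixed-model repeated-measures analyses having a maximum likelihood estimation will be used to analyze changes in cognitive performance". Its treatment term is "randomization group (dichotomous variable coded as 0 for control and 1 for intervention"). The other listed terms are time, "characteristic, and group × time × characteristic interaction". No four-level group factor, arm-specific contrast or comparison of one active arm with another appears in the protocol.

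**The concern.** One two-level variable cannot represent a four-arm allocation unless arms are merged. If everyone not in control is coded 1, the model compares control with a mixture of three treatments.

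Two things are lost. The Aim asks about the full package, and the coefficient is not the effect of that package; it understates that effect whenever the other two active arms do less on average. The nested design also exists to separate the contributions of diet and exercise, and the model has no term for either. The trial would bear the cost of three distinct active arms and report one averaged figure. A reader could take that figure for the multimodal effect.

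**Working it through.** **Inputs from the protocol.** Four arms, 1:1:1:1 (Study Design); 15 evaluable per arm, 10% dropout, 17 per arm and 68 in total (Sample Size); group coded 0/1 (Analysis Plan).

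**Assumed, because the protocol does not give them.** Effects versus control in SD units of the outcome analysed; a common SD of 1 in those units; normal-approximation 95% intervals.

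**1. The protocol's own figure.** 15 / 0.9 = 16.7, rounded up to 17; 17 × 4 = 68. This reproduces exactly and confirms that the protocol itself counts four groups.

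**2. What the 0/1 coefficient estimates.** Let e1, e2 and e3 be the effects of CBCT, CBCT plus diet, and CBCT plus diet plus exercise versus control. With equal arms the coefficient is (e1 + e2 + e3) / 3.

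| Assumed e1 / e2 / e3 (SD) | 0/1 coefficient | Share of e3 |
|---|---|---|
| 0 / 0 / 0.8 | 0.27 | 33% |
| 0.2 / 0.4 / 0.8 | 0.47 | 58% |
| 0.4 / 0.6 / 0.8 | 0.60 | 75% |
| 0.6 / 0.7 / 0.8 | 0.70 | 88% |

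**3. Different truths, same answer.** Effects of 0.2 / 0.4 / 0.8 give 1.4 / 3 = 0.467. The multimodal effect is 0.8, diet adds 0.4 − 0.2 = 0.2 and exercise adds 0.8 − 0.4 = 0.4. Effects of 0.8 / 0.4 / 0.2 also give 0.467, but the multimodal effect is then 0.2, diet adds 0.4 − 0.8 = −0.4 and exercise adds 0.2 − 0.4 = −0.2. The planned model cannot tell these apart. In matrix terms the 0/1 design has rank 2 (intercept and one contrast) and the four-level design has rank 4 (intercept and three contrasts).

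**4. Precision.**
- Two arms, 15 v 15: SE = √(1/15 + 1/15) = 0.365 SD; 95% half-width 1.96 × 0.365 = 0.72 SD.
- Pooled, 45 v 15: SE = √(1/45 + 1/15) = 0.298 SD; half-width 1.96 × 0.298 = 0.58 SD.
- Ratio 0.365 / 0.298 = 1.22.

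**5. Does the smaller SE make up for the averaging?** Effect divided by SE for the full package versus control is 0.8 / 0.365 = 2.19 in every row of the table. For the pooled contrast it is 0.89, 1.57, 2.01 and 2.35 in turn. Pooling gains only when the average active effect exceeds 0.298 / 0.365 = 82% of the multimodal effect, as in the last row. Even then it estimates a different quantity.

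**The case against.** The strongest reply is that the Analysis Plan never says the active arms are pooled. The 0/1 code could be used in turn for each active arm against control, and Study Design itself speaks loosely of a single intervention group just after listing three. On that reading the multimodal effect would be estimated. But the text does not say so: it defines one variable with two levels and gives no rule for restricting the data. Even that reading includes no direct comparison between active arms.

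A statistical analysis plan, not seen here, might add contrasts. That limits the finding to the model as the protocol states it. It does not cure it, because the protocol does not leave the coding open, and a four-level plan would contradict it.

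Three further points stand:
- The Aim does not name the added value of diet or of exercise as an objective. That is inferred from the nested arms, so the mismatch with the multimodal aim is the firmer part of the finding.
- Dilution is conditional. It occurs only if the other two arms do less on average than the full package, and pooling can be the more sensitive test when all three work about equally well.
- This is a pilot sized on feasibility. No power claim is broken, and contrasts between two arms will be imprecise.

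**Conclusion.** The plan is wrong as written. Study Design and Sample Size have four groups and the Analysis Plan has two, and the stated model does not estimate the effect named in the Aim. That conclusion follows from the text and needs no assumed effect size.

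The size of the discrepancy does depend on assumptions. Across the illustrative patterns with a multimodal effect of 0.8 SD, the 0/1 coefficient ranges from 33% to 88% of that effect; it equals the effect only if the three arm effects average to it. That the diet and exercise increments cannot be recovered from this model holds whatever the effects are. The absolute standard errors assume 15 evaluable per arm and a common SD; the 1.22 ratio needs only equal arms and a common SD.

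**What to change.** Rewrite the model in the Analysis Plan before outcome data are seen:

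- Enter randomised group as a four-level factor with control as reference.
- Add the two-way group by time term. The current list has only the three-way interaction, so recoding group alone would not give a treatment effect on change.
- Name CBCT plus diet plus exercise versus control, group by time at 6 months, as the single primary contrast.
- Report CBCT versus control, CBCT plus diet versus CBCT, and CBCT plus diet plus exercise versus CBCT plus diet as secondary estimates with 95% confidence intervals.
- Label any pooled active-versus-control contrast as supportive.

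Arms, visits, data collection and the total of 68 are unchanged. The primary contrast has a standard error about 22% larger than the pooled one, with a half-width near 0.72 SD, so results should be presented as pilot estimates. A four-level factor also turns each three-way interaction with a characteristic from one coefficient into three. At 15 per arm these should be fitted separately from the primary model and called exploratory.

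### The protocol's only stated model lists group × time × characteristic without group × time, so as written it has no coefficient for the overall 6-month effect and can present a uniform benefit as effect modification

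*Protocol*

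**What the plan says.** The Aim is an intervention effect: "To study the effect of multimodal intervention" on cognition. Under Outcomes, "The primary outcome will be measured after 6 months by evaluating change in cognitive performance", with the PGI Memory Scale total as the measure.

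The Analysis Plan offers one inferential method: "Mixed-model repeated-measures analyses having a maximum likelihood estimation will be used to analyze changes in cognitive performance". Three kinds of explanatory term follow:

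- Allocation enters as a single indicator: "randomization group (dichotomous variable coded as 0 for control and 1 for intervention".
- Visit enters as a numeric variable that starts at zero; the value for the second visit is not given.
- The list then closes with "characteristic, and group × time × characteristic interaction".

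The section then defines the characteristics. Three are dichotomous ("The characteristics will be either dichotomous (sex, presence of nutritional risk, and deterioration in quality of life") and nine are "continuous variables (age, education level, scores on the following scales: MMSE, Mini-Cog, BADL, IADL, GDS-15, SF-36, and MNA", so twelve in all.

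The section does not list group × time, group × characteristic or time × characteristic. It does not state a model without a characteristic, and it does not tie any model to the PGI Memory Scale total.

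**The concern.** With a baseline and a 6-month visit, the treatment effect on change is the group × time term. The listed model omits it and carries group and time jointly only through the three-way product with a characteristic. That is the form of an effect-modifier analysis, with the terms beneath the interaction left out.

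Two things are at stake. First, the protocol states no estimator for its main question. Second, if the list is fitted as it stands, a real and uniform benefit has to go into the terms that remain: partly the common time slope, partly a spurious baseline group difference, and partly the three-way term, where it would be read as modification by whichever characteristic is in the model.

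**Working it through.** **The plan's own figure.** The only design figure is the sample size: 15 / (1 − 0.10) = 16.67, rounded up to 17, and 17 × 4 = 68. It reproduces and this point does not affect it.

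**Algebra of the listed terms.** Let g = 0/1 for group, t = 0 at baseline and 1 at 6 months, and c = the characteristic:

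E[Y] = b0 + bG·g + bT·t + bC·c + b3·g·t·c

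- Change in control: bT
- Change in intervention: bT + b3·c
- Between-group difference in change: b3·c

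If c is coded 0/1, the difference is zero by construction where c = 0. If c is raw age, it is forced to be proportional to age. The coefficient bG is only the baseline difference, which randomisation makes zero in expectation. No coefficient is the overall effect.

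**Inputs for size.** From the protocol: 15 evaluable per arm, one control and three active arms, and one 0/1 group variable. Pooling the active arms under that variable gives 15 against 45. Assumed, because the protocol gives no values: outcome SD 1, visit correlation 0.6 (0.4 to 0.8 as a range), random subject intercept, characteristic coded 0/1 and split 50/50, the same effect in every active arm, and no true modification.

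**Expected coefficients.** The large-sample fit is b = (Σ w·X′V⁻¹X)⁻¹ Σ w·X′V⁻¹μ. The sum runs over the group-by-characteristic cells with weights w, V is the two-visit correlation matrix and μ holds the true means. With a true effect of 1.0 and a true control change of 0.2:

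| Design | Correlation | Three-way (true 0) | Group (true 0) | Time (true 0.2) |
|---|---|---|---|---|
| Three active arms pooled | 0.4 | 0.368 | 0.408 | 0.812 |
| Three active arms pooled | 0.6 | 0.381 | 0.405 | 0.807 |
| Three active arms pooled | 0.8 | 0.391 | 0.402 | 0.803 |
| Two equal groups | 0.4 | 0.583 | 0.354 | 0.554 |
| Two equal groups | 0.6 | 0.615 | 0.346 | 0.546 |
| Two equal groups | 0.8 | 0.643 | 0.339 | 0.539 |

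The bias hardly depends on the assumed correlation. It scales with the effect, so for 0.8 SD, pooled arms and correlation 0.6:

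- Three-way: 0.8 × 0.381 = 0.305 (truth 0)
- Group: 0.8 × 0.405 = 0.324 (truth 0)
- Time beyond the true control change: 0.8 × (0.807 − 0.2) = 0.486 (truth 0)
- Average fitted difference in change: 0.5 × 0 + 0.5 × 0.305 = 0.15 (truth 0.8)

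**False rejection of the three-way term.** Simulation with maximum likelihood and a 1.96 cut-off, 15 against 45, 0/1 characteristic. Ranges cover separate simulation runs.

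| True uniform effect | Listed terms | All lower-order terms added |
|---|---|---|
| 0 | about 6% | about 7% |
| 0.5 SD | 11–15% | about 7% |
| 0.8 SD | 22–24% | about 6% |

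The right-hand column is the fair comparator. It sits slightly above 5% because of the small sample and the normal cut-off.

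**Continuous characteristics.** For raw age (assumed mean 68, SD 6), the listed terms reject in 47% of trials at 0.5 SD and 84% at 0.8 SD, against 6–8% for the full model. The fitted effect at age 68 is then 0.98 of the truth, so the effect is mislabelled as modification by age but not lost. With centred age there is no excess (about 5%), but the listed model then has no term for the average effect.

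**The case against.** The strongest reply is that the sentence is visibly broken: the parenthesis opened at the coding of time never closes, and no code is given for the 6-month visit. Words may have been lost. A highest-order interaction is also often written as shorthand for the whole hierarchy, and STATA, which the protocol names, has interaction syntax that expands that way. This stands. A reader might infer that the authors deliberately left group × time out; the text does not establish that. Under the shorthand reading the false modification disappears. What remains is an effect-modifier model that could be fitted with each of twelve characteristics, with no overall-effect model stated.

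A reader might also infer that the trial has no main analysis at all. The protocol does not call this model primary, and the unseen SAP may contain a separate one. The supportable statement is narrower: the only model that the protocol itself gives does not answer its primary question.

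Nor is the lack of centring a further error. Once the lower-order terms are present, centring changes only the parameterisation; the fit is the same, and the effect at any value of the characteristic is a linear contrast.

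Finally, this is a pilot sized by feasibility, and no document supports an effect as large as 0.8 SD. That limits the weight of the percentages but does not affect the algebra.

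**Conclusion.** The point holds for the protocol as written. The listed terms contain no estimator of the overall 6-month effect, and they force that effect to zero where a 0/1 characteristic is 0. That part is algebra and rests only on reading the list literally with 0/1 coding.

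The size is conditional. With three active arms pooled (15 against 45), correlation 0.6 and a 50/50 characteristic, false effect modification is found in about 11–15% of trials at 0.5 SD and 22–24% at 0.8 SD, against about 6–8% for the full model. A reader might infer that false modification is inevitable. It is not: it needs a real treatment effect together with a 0/1 or uncentred characteristic, and there is no excess when treatment does nothing.

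If the full hierarchy was intended, the remaining defect is that the protocol states no model for the overall effect on the PGI Memory Scale total.

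**What to change.** In the Analysis Plan, state the primary model for the PGI Memory Scale total as arm + time + arm × time with a subject random effect and no characteristic. Name the 6-month arm × time contrast as the treatment effect.

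Describe the characteristic models separately as exploratory, and say that each includes group × time, group × characteristic and time × characteristic beneath the three-way term. Mean-centring the continuous characteristics is optional and only makes the coefficients easier to read. Repair the broken sentence at the same time, including the code for the 6-month visit.

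The cost is protocol and SAP wording only. Sample size, visits and data collection do not change.
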